## Methods/Design

### Study design

A three-armed randomized controlled trial (RCT) will be conducted. Participants will be randomly allocated to one of three conditions: a) *Transdiagnostic Internet-based protocol (TIBP)*, b) *Transdiagnostic Internet-based Protocol + Positive Affect component (TIBP + PA),* and c) *Waiting List control condition (WL)*. For ethical reasons, participants in the control condition will be offered the possibility of receiving the treatment protocol. Block randomization will be performed within each stratum in order to ensure that all primary diagnoses are equally represented across conditions. Measures will be taken at post-randomization, after the treatment, and at 3- and 12-month follow-ups, in order to test whether the improvements achieved during the therapy are maintained in the long term.The study flowchart is shown in Fig. 1. The study will be conducted following the CONSORT statement (Consolidated Standards of Reporting Trials, http://www.consort-statement.org) [57, 58] the CONSORT-EHEALTH guidelines [59], and the SPIRIT guidelines (Standard Protocol Items: Recommendations for Interventional Trials) [60, 61].

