### Sample size

To determine the sample size, the effect sizes found in the literature have been considered. An RCT using the UP in a traditional face-to-face approach [33] obtained effect sizes of 0.56 for anxiety, measured with the BAI, and 1.11 for depression, measured with BDI-II. The mean effect size indicated in a recent meta-analysis [39] comparing transdiagnostic computerized cognitive-behavior therapy (CBT) to waitlist control was g = .93 for anxiety and g = .88 for depression.

Adopting a more conservative approach than those of the aforementioned studies, we assumed an effect size of 0.5 (Hedges’ g), which, following Cohen [62], can be considered an effect size of medium magnitude. As our design included three experimental conditions (*TIBP*, *TIBP + PA*, *WL*), a between-groups one-way ANOVA was assumed for the statistical analyses. Therefore, calculations of the necessary sample size cannot be based on Hedges’ *g* index for effect size, but rather on the *f* index [62]. Following Cohen [62], *f* = 0.25 represents an effect size of medium magnitude (and equivalent to *g* = 0.5). Thus, considering an alpha of .05 and a statistical power of .80, the total sample size required to warrant these conditions contains 159 participants (53 participants per group). To control the maximum possible loss of subjects during treatment, based on the literature about Internet-based treatments, a 30% dropout rate is expected [53, 63]. Thus, the required sample size should have 207 participants in all (69 participants per group). These calculations were accomplished with the software program *G*Power 3.1* [64].

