### Study population, recruitment and eligibility criteria

The clinical trial will be conducted in a community sample of patients diagnosed with the aforementioned disorders. Participants will be adult volunteers who contact us because they are interested in the study (personal visits or phone calls to the emotional disorders university clinic, emails, or leaving their data on a website specially prepared for this purpose). Potential participants will be attended to by a psychologist who will describe the study characteristics to them. All the psychologists working on this study will have at least a master’s degree in Clinical Psychology, with experience in the diagnosis, psychological assessment, and application of EBTs for ED.

The psychologist will clarify any doubts, ensure that the participant has read the information about the study, and make sure that s/he has understood the three experimental conditions. People interested in participating will sign an online informed consent and be assessed taking into account all the inclusion criteria. Inclusion and exclusion criteria are shown in Table 1. If the patient fulfills all the study criteria, the researcher will contact an independent researcher to implement randomization. This researcher will be unaware of the characteristics of the study. Randomization will be performed using weighted random allocation [65] in order to take into account the clinical features (different diagnoses) and, thus, obtain a homogeneous distribution in the three experimental conditions. Participants agree to participate before finding out to which treatment they will be allocated. All participants will be free to withdraw from the treatment at any time.

**Table 1 Tab1:** Inclusion and exclusion criteria

Inclusion criteria	Exclusion criteria
Minimal age of 18 years	Suffering from Schizophrenia, bipolar disorder, or alcohol and/or substance dependence disorder
Meeting the DSM-IV diagnostic criteria for ED	High risk of suicide
Ability to understand and read Spanish	Medical disease/condition that prevents the participant from carrying out the psychological treatment
Access to Internet at home and having an email address	Receiving another psychological treatment during the study
Providing online informed consent	An increase and/or change in the pharmacological treatment (in the case of receiving) during the study period

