### Data analyses

Intention-to -treat analyses and per protocol analyses will be performed, and CONSORT recommendations will be followed [98]. First, the three groups will be compared to verify that there are no significant differences among them at baseline on the outcome measures in order to confirm that they are comparable after randomization. One-way ANOVAs for continuous variables and Chi-squared tests of independence for categorical ones will be used. For the continuous outcome measures on the posttest, the homoscedasticity assumption will be assessed with the Levene test. Where this assumption is met, the usual *F*-test will be applied to compare the posttest means for the three experimental conditions. If the homoscedasticity assumption is not met, the Brown-Forsythe *F*-test will be applied. Statistically significant *F*-tests will be followed by post hoc comparisons. In particular, the Tukey procedure will be applied where the homoscedasticity assumption is met, and the Games-Howell procedure if this assumption is not met.

The intention-to-treat principle will be used when analyzing primary and secondary post-treatment data and data collected at the 3- and 12-month follow-ups, using mixed-effect models with full information maximum likelihood estimation. This method has been recommended due to its flexibility on repeated-measures ANOVAs in handling missing data more appropriately [99]. To complement the results of the ANOVAs and post hoc comparisons, effect sizes will be calculated by using the standardized mean difference proposed by Cohen [62]. These effect sizes will be calculated to assess both within- and between-group changes, all of them based on a pooled standard deviation.

Although per protocol analyses (completers only analysis) suffer from selection bias, they will also be conducted to help to draw conclusions about the maximum treatment efficacy in patients who comply fully with the treatment [100].

When the trial ends, the analytic methodology for the RCT will be reviewed before analyzing the data in order to select the most appropriate analytic procedures.

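### Allocation is described in two unlinked ways, both balancing primary diagnosis, and the posttest ANOVA leaves diagnosis out, at a modest cost in precision

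*Protocol article*

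**What the plan says.** The protocol article describes allocation twice. Under Study design: "Block randomization will be performed within each stratum in order to ensure that all primary diagnoses are equally represented across conditions". Under Study population, recruitment and eligibility criteria: "Randomization will be performed using weighted random allocation". That second sentence cites a reference, gives the different diagnoses as the reason for the method, and states as its aim to "obtain a homogeneous distribution in the three experimental conditions".

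The Sample size section uses a model with condition as the only factor: "a between-groups one-way ANOVA was assumed for the statistical analyses". Data analyses keeps to this for posttest outcomes. Where variances are equal, "the usual *F*-test will be applied to compare the posttest means for the three experimental conditions". The fallback is also a comparison of arms only: "If the homoscedasticity assumption is not met, the Brown-Forsythe *F*-test will be applied". Post hoc tests are Tukey or Games-Howell. None of these has a diagnosis term.

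Data analyses also plans mixed-effects models with full information maximum likelihood for the intention-to-treat analysis of post-treatment and follow-up data. Their fixed effects are not listed. The section ends by saying that the analytic methods will be reviewed once the trial is over and before the data are analysed.

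**The concern.** There are two linked issues.

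First, one step carries two method names. Block randomisation within strata and a weighted allocation are not the same procedure by name, and a reader cannot tell which was meant, whether one is a loose label for the other, or which diagnoses form the strata. The choice matters for the analysis too, because it defines the factor that the analysis should reflect.

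Second, both descriptions agree that primary diagnosis is balanced on purpose. Balance removes differences between diagnoses from the comparison of arms. A one-way ANOVA nevertheless leaves those differences in its error term, so its standard errors describe a noisier design than the one that was run. The eligible diagnoses span depressive, anxiety and obsessive-compulsive disorders, so BDI-II, BAI and PANAS scores can reasonably be expected to differ between them. At stake is some power that the allocation has already made available.

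**Working it through.** **Allocation text, side by side.** Study design: blocks within each stratum, so that primary diagnoses are equally represented. Study population: weighted random allocation, so that diagnoses are evenly distributed over the three conditions. The aim is the same, the method names differ, and no sentence connects them.

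**Inputs from the documents.** Three arms of equal size; f = 0.25; alpha 0.05; power 0.80; 159 before dropout; 30% dropout; 207 to be randomised (all Sample size). Nine diagnoses are listed under Interventions; the number of strata is not stated.

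**Assumptions.** R² is the share of posttest variance explained by diagnosis. The documents give no figure, so I take 0.05, 0.10 and 0.15, with 0 as the reference. I take nine strata, so a diagnosis factor uses 9 − 1 = 8 degrees of freedom.

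**The plan's own figure.** For a one-way ANOVA, power comes from the noncentral F with λ = N·f² and (2, N − 3) degrees of freedom. At N = 159, λ = 159 × 0.0625 = 9.94 and power is 0.805. At N = 156 it is 0.797. The stated 159 reproduces.

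**Number analysed.** 207 × 0.70 = 144.9, taken as 144 (48 per arm). This is below 159 because 207 is 159 × 1.3 and not 159 / 0.7; that is a separate matter.

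**Analytic comparison at N = 144.** Unadjusted: λ = 144 × 0.0625 = 9.00, df (2, 141). Adjusted: λ = 9.00 / (1 − R²), df (2, 144 − 3 − 8) = (2, 133). The ratio of unadjusted to adjusted standard error is 1/√(1 − R²).

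| R² | λ adjusted | Power unadjusted | Power adjusted | Excess in standard error |
|---|---|---|---|---|
| 0 | 9.00 | 0.761 | 0.761 | 0% |
| 0.05 | 9.47 | 0.761 | 0.783 | 2.6% |
| 0.10 | 10.00 | 0.761 | 0.806 | 5.4% |
| 0.15 | 10.59 | 0.761 | 0.829 | 8.5% |

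On this formula the gain is about 2 to 7 points. It is somewhat too generous: the unadjusted figure takes no account of the stratified allocation, and the adjusted one assumes exact balance within strata among those analysed, which dropout disturbs.

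**Simulation closer to the design.** 207 randomised in blocks of three within nine equal strata, 30% random dropout, f = 0.25, 6,000 replicates per setting:

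| R² | Power unadjusted | Power adjusted |
|---|---|---|
| 0.05 | 0.77 | 0.78 |
| 0.10 | 0.76 | 0.80 |
| 0.15 | 0.76 | 0.81 |

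The gain is about 1 to 5 points.

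**Direction of the error.** In the same design the unadjusted test has a type I error of about 0.050 at R² = 0, falling to about 0.036 at R² = 0.15. Without dropout (N = 159, 20,000 replicates) the unadjusted error is 0.049, 0.042, 0.038, 0.025 and 0.014 at R² = 0, 0.05, 0.10, 0.20 and 0.30, while the adjusted test stays between 0.050 and 0.052. Leaving diagnosis out makes the test conservative.

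**The case against.** The best defence has four parts.

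- **The two descriptions may be compatible.** A reader might infer that the weighted method shifts allocation probabilities according to earlier assignments, and so cannot coexist with blocks. The article does not say this; it only cites a source that is not shown, and it gives both methods the same aim. This part stands: the text supports two unlinked labels, not two procedures proved incompatible. A condensed article may leave the mechanics to a full protocol, but it should not name the step in two ways without a link.
- **The ANOVA is not the only analysis.** A reader might infer that the whole analysis ignores diagnosis. It does not follow: the intention-to-treat analysis uses mixed-effects models whose fixed effects are unlisted, and such detail is commonly left to an analysis plan. This stands, and the point is limited to the posttest ANOVA. The Sample size section's one-way model is likewise an ordinary and conservative planning assumption.
- **The size is assumed.** The gain depends on an R² and a number of strata that the documents do not give. This stands, which is why a range is shown.
- **Methods will be reviewed before analysis.** This helps little. The sentence names no diagnosis term, and a review after the trial cannot clarify an allocation procedure already carried out.

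**Conclusion.** The point holds in limited form. The two allocation descriptions need reconciling, and the stated posttest tests (F or Brown-Forsythe, then Tukey or Games-Howell) omit the factor on which allocation is balanced.

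The cost is lost precision: roughly 1 to 5 power points if diagnosis explains 5% to 15% of posttest variance, with about 144 analysed, nine strata and dropout unrelated to outcome. If diagnosis explains nothing, adjusting changes power by almost nothing.

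Two stronger conclusions are tempting and unsupported. Omitting the factor does not raise the false-positive rate; it lowers it. Nor does it make the pre-dropout sample size wrong, since 159 reproduces for the one-way test and remains adequate with diagnosis in the model (power 0.804 at R² = 0, and higher as R² rises).

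**What to change.** Name one allocation method in both Study design and Study population, recruitment and eligibility criteria, and list the diagnosis strata it uses. If both terms describe one procedure, say so in a sentence.

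In Data analyses, add primary diagnosis, as used in the allocation, as a fixed factor in the posttest comparison of arms, pooling rare diagnoses if the model needs it. Carry the same term into the mixed-effects intention-to-treat model so that the two analyses agree.

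The cost is a few sentences and one model term, with no new data. Up to 8 error degrees of freedom are spent. The Brown-Forsythe and Games-Howell fallbacks have no place for a second factor as planned, so they would need a covariate-adjusted equivalent, such as the same linear model with heteroscedasticity-robust standard errors.

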### Adaptation to the web

This protocol has been adapted to a multimedia web platform (video, images, etc.) and can be applied over the Internet (https://www.psicologiaytecnologia.com/). It is developed for optimal use on a PC or a tablet, and it allows individuals to do the modules from their home and at their own pace. The ease of use of the program has been strengthened because it presents a streamlined navigation, which allows users with less experience in handling new technologies to know where they are and how to keep moving forward at any time. The web adaptation of the protocol is the same in both conditions (TIBP and TIBP + PA), with the only difference being the inclusion or not of the modules that contain the PA-regulation component.

Duration of the program can vary among users, and participants in both treatment conditions have access to the protocol for a maximum period of 18 weeks. The program recommends working on one module for at least one entire week, and it sends messages encouraging the patient to continue to work to benefit from it. In both conditions, the modules include exercises and tasks to practice each technique and skill. Moreover, the platform is ready to welcome all participants with information about the treatment and its objectives, as well as general information and recommendations about how to benefit from it.

Regarding the assessment of patients within the program, after the “Welcome”, initial online questionnaires are presented as the pre-treatment assessment. In addition, post-module brief questionnaires to evaluate anxiety, depression, and positive/negative affect (OASIS, ODSIS, PANAS) are also filled out throughout the program. A noteworthy aspect of the program is that it allows the therapist to have access to all this information and receive an alert if the patient’s condition worsens. The program includes suicide risk alarms that consist of an email to the clinical team with information about a high risk of suicide. These alarms are generated when the system detects that the participant rated high on the suicidal ideation items. It allows the clinician to contact the patient and evaluate the actions that should be taken to protect him/her. Finally, after the treatment, the participants complete the online assessment in the post- and follow-up periods.

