#### Expectation of treatment scale and opinion of treatment scale.

The Expectation of Treatment Scale and Opinion of Treatment Scale are questionnaires adapted from Borkovec and Nau [96]. Each scale contains five items, rated from 0 (“strongly disagree”) to 10 (“strongly agree”), which cover how logical the treatment seemed, to what extent it could satisfy the patient, whether it could be used to treat other psychological problems, and its usefulness for the patient’s specific problem. The expectation scale is applied once the intervention has been explained, at the end of the “Welcome module”. This scale measures the patient’s subjective expectations about the treatment. In addition, the opinion scale is administered when the patient has completed the treatment, and its aim is to assess satisfaction with the intervention. Our group has used this questionnaire in several research studies [48, 97].

The study measures and assessment times are summarized in Table 2.

**Table 2 Tab2:** Study measures and assessment times

Measure	Aim	Time of assessment
MINI Neuropsychiatric Interview	Diagnosis	BL, Post-T and FU
PANAS	Positive and negative affect	Post-T and Post-module
BDI-II	Severity of depression	BL, Post-T and FU
BAI	Severity of anxiety	BL, Post-T and FU
OCI-R	Severity of OCD symptoms	BL, Post-T and FU
PDSS-SR	Severity of PD and agoraphobia symptoms	BL, Post-T and FU
PSWQ	Severity of GAD symptoms	BL, Post-T and FU
SIAS	Severity of SAD symptoms	BL, Post-T and FU
NEO FFI	Neuroticism and Extraversion	BL, Post-T and FU
EQ-5D	Health-related quality of life	BL, Post-T and FU
OASIS	Severity of anxiety	Post-module
ODSIS	Severity of depression	Post-module
Suicide item	Suicidal ideation	BL, Post-module, Post-T and FU
Expectation of Treatment Scale	Expectation of treatment	BL
Opinion of Treatment Scale	Opinion of treatment	Post-T

*BL*, Baseline; *Post-T*, post-treatment; *FU*, follow-ups, 3 and 12-month follow-ups; *PANAS*, Positive and Negative Affect Scale; *BDI-II*, Beck Depression Inventory-II; *BAI*, Beck Anxiety Inventory; *OCI-R*, Obsessive-Compulsive Inventory-Revised; *PDSS-SR*, Self-Reported Panic Disorder Severity Scale; *PSWQ*, Penn State Worry Questionnaire; *SIAS*, Social Interaction Anxiety Scale; *NEO FFI*, NEO-Five Factor Inventory; *EQ-5D*, EuroQoL-5D questionnaire; *OASIS*, Overall Anxiety Severity and Impairment Scale; *ODSIS*, Overall Depression Severity and Impairment Scale

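### The questionnaire baseline is placed after randomisation and, in the active arms, after the programme has explained the treatment, so baseline scores can already reflect knowledge of the arm

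*Protocol article*

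**What the plan says.** All references are to the protocol article.

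- **Study design** gives the measurement schedule: "Measures will be taken at post-randomization, after the treatment, and at 3- and 12-month follow-ups".
- **Study population, recruitment and eligibility criteria** puts consent and the assessment against the inclusion criteria first. Then: "If the patient fulfills all the study criteria, the researcher will contact an independent researcher to implement randomization". On disclosure it says only: "Participants agree to participate before finding out to which treatment they will be allocated".
- **Adaptation to the web** says that, after the Welcome, "initial online questionnaires are presented as the pre-treatment assessment". It also says that "the platform is ready to welcome all participants with information about the treatment and its objectives". Access is described for the treated arms: "participants in both treatment conditions have access to the protocol for a maximum period of 18 weeks".
- **Expectation of treatment scale and opinion of treatment scale** fixes the timing of one measure that Table 2 lists at baseline: "The expectation scale is applied once the intervention has been explained, at the end of the" Welcome module.
- **Ethics** offers the waiting-list (WL) arm the intervention once the waiting time has ended.
- **Data analyses** uses baseline for a between-arm comparability test and for within- and between-group change effect sizes. It also plans an F-test on posttest means, which uses no baseline, and mixed-effect models for the intention-to-treat analysis.

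**The concern.** A baseline score should be fixed before anything that differs between arms can touch it. Here the stated order is eligibility, randomisation, then questionnaires. In the active arms the questionnaires come after the participant has entered the treatment programme and been told what the treatment is for. Nobody is blinded to having or not having treatment, and the three primary instruments are self-reports. Relief at being treated, or disappointment at being put on a waiting list, could move the scores before the pre-treatment value is recorded.

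Any analysis that subtracts or adjusts for baseline would then remove, or add, part of an effect of allocation. A baseline comparison meant to confirm that randomisation produced comparable groups could not cleanly do so, because the scores would no longer depend on chance alone.

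**Working it through.** **1. Is the order really fixed this way?** Set the sections side by side.

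- Study design names the first measurement point as after randomisation.
- Adaptation to the web agrees: a participant who answers inside the treatment programme has already been allocated to treatment.
- The Expectation scale supports this. It is a baseline measure in Table 2 and is given when the intervention has already been explained.
- The Abstract says only that participants are assessed pre-treatment. That is compatible with either side of randomisation.
- No section places the outcome questionnaires before allocation.

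The two main sections therefore agree, and the point does not hang on one loose word.

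**2. What the powered test uses.** The plan's own figure is 159 participants (53 per group), for a three-group one-way ANOVA with f = 0.25, alpha .05 and power .80. With noncentrality N × f², N = 159 gives 159 × 0.0625 = 9.94 on 2 and 156 degrees of freedom, and power 0.805. N = 156 gives 0.797. The figure of 159 reproduces. The matching test in Data analyses compares posttest means and contains no baseline term, so a baseline shift moves it by zero.

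**3. How a shift would pass into the other analyses.** Let s be the difference in baseline, in SD, between the active arms and WL that is caused by knowing the arm. Assume equal SDs at both times and no effect of the shift on the posttest score.

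- Posttest-only contrast: moves by 0.
- Change-score contrast: moves by s.
- Baseline-adjusted contrast: moves by slope × s.

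**4. Illustration only.** Neither s nor the slope is in the documents. Assume s = 0.1 to 0.3, a slope of 0.3 to 0.7 and a true posttest difference of 0.5 SD.

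| Contrast | Active arms report lower baseline symptoms | WL reports lower baseline symptoms |
|---|---|---|
| Posttest only | 0.50 | 0.50 |
| Change score | 0.5 − 0.1 = 0.40 to 0.5 − 0.3 = 0.20 | 0.60 to 0.80 |
| Baseline-adjusted | 0.5 − 0.3 × 0.1 = 0.47 to 0.5 − 0.7 × 0.3 = 0.29 | 0.53 to 0.71 |

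The sign depends on which arm reacts, and the documents give no guide to that. Nor does s fix the error within an arm. If the active arms shift by a and WL by w, then s is the difference between a and w, and either one may be zero. The within-group effect sizes cannot be given a range from s alone.

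**5. Would the planned baseline test catch it?** With both active arms shifted by s against WL, f = s × √2 / 3. For s = 0.1, 0.2 and 0.3 this is 0.047, 0.094 and 0.141. At N = 207 and alpha .05 the power is 0.09, 0.21 and 0.42. A non-significant baseline ANOVA would be weak reassurance against shifts of this order.

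**6. Which comparisons are reached.** TIBP and TIBP + PA share the same web adaptation apart from the positive-affect modules, so the setting gives no reason for their baselines to differ. The exposure lies mainly in active versus WL, and in pre-post change within an arm.

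**The case against.** The strongest reply is that this is a wording question in a condensed article with little consequence for the main test. Much of that stands.

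- The F-test that sizes the trial uses posttest means only and is untouched. A reader might infer that the planned 0.5 SD comparison is itself biased by some percentage. That is not supported: the 0.5 belongs to the test with no baseline in it, and no ANCOVA is specified.
- The mixed model is described for post-treatment and follow-up data, and how it treats baseline is not stated. It is exposed only if baseline enters it.
- Not everything labelled baseline need follow randomisation. The MINI is presumably done at the eligibility assessment, and that section does not list its instruments.
- The moment of disclosure is not given, and the participant flowchart (Fig. 1) is not visible and could show a different order.
- A reader might also infer that WL completes its baseline in a different setting, that anyone who never logs in has no baseline, and that intention-to-treat is therefore undermined. The article says none of this. It is silent on how WL completes its forms, and a condensed article may leave that to the full protocol. Full information maximum likelihood need not exclude a participant with a missing baseline if baseline is modelled as a repeated outcome.

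What the reply does not remove is the affirmative statement of order, made in two sections that agree. It is not a silence that another document would fill.

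**Conclusion.** The point holds in limited form. As written, the questionnaire baseline follows randomisation and, for the active arms, follows the programme's explanation of the treatment. With open allocation and self-reported primary outcomes, baseline can already reflect the arm. That it does so is not shown.

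Four uses are exposed: the comparability check, the change effect sizes, the pre-post improvement claimed in hypothesis b, and any mixed model that uses baseline. The posttest F-test is not exposed, and hypothesis c (TIBP + PA against TIBP) is largely untouched.

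Size and direction cannot be derived from the documents. The figures in the table rest wholly on the assumed shift and slope and show the mechanism only. The conclusion assumes that participants know their arm when they answer, and that Fig. 1 does not show another order. The change is worth making because it closes off a source of bias at almost no cost, but the trial's main test does not depend on it.

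**What to change.** Amend Study design and Adaptation to the web so that BDI-II, BAI, PANAS, the diagnosis-specific scale, NEO-FFI and EQ-5D are completed online, in the same way in all three arms, after consent and confirmed eligibility and before the independent researcher is asked for an allocation. Keep only the Expectation scale after allocation, since it needs the treatment to have been explained. Table 2 should then also show a baseline time for the PANAS, which it now lists only at post-treatment and post-module although the Abstract has participants assessed pre-treatment on the primary outcomes.

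If the questionnaires are already completed before allocation, correct the two sections so that they state this order.

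The cost is a reordering of existing online forms, with no new measure, visit or change in sample size. A few people may be lost before randomisation rather than after it.
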